## Methods

### Study purpose

(1) Primary purpose: To investigate neurologic function in the early postoperative period for patients with supratentorial intracranial gliomas under inhalational general anesthesia compared to intravenous general anesthesia. The hypothesis is that the difference in postoperative National Institute of Health Stroke Scale (NIHSS or modified NIHSS) score changes under the two general anesthesia methods are not different, with the score difference within − 1 to 1.

(2) Secondary purpose: To compare the effects of inhalational general anesthesia versus intravenous general anesthesia on neurocognition, hemodynamics, cerebral physiology, anesthesia recovery quality, pain scores, anesthesia expenses, and stress responses in patients with supratentorial intracranial gliomas undergoing elective craniotomy.

### Trial design

The study is a prospective, single-center, open label, randomized parallel arm equivalent clinical trial comparing sevoflurane and propofol, both combined with remifentanil, general anesthesia (Sevoflurane-remifentanil versus Propofol-remifentanil group) in patients with supratentorial gliomas; it will be carried out in the neurosurgical operation room in Beijing Tiantan Hospital (a large city), Capital Medical University, Beijing, China.

### Populations

Adult male and female patients scheduled for elective craniotomy under general anesthesia with supratentorial (frontal-parietal-temporal) gliomas diagnosed by magnetic resonance imaging (MRI) are eligible for the study. All patients must sign institutional approval and informed consent before enrollment, the written informed consent will be obtained 1 day or a few days before operation, when patients are seen by anesthesiologists in the ward. The information and reasons why eligible patients are not recruited to the trial will be documented. The inclusion and exclusion criteria are listed in Table 1.

**Table 1 Tab1:** Inclusion and exclusion criteria

Inclusion Criteria	
Patients aged between 18 to 65 years old with American Society of Anesthesiology (ASA) status I ~ II who are scheduled for elective craniotomy for the treatment of supratentorial gliomas must fulfill the following:	
1	Frontal-Parietal-Temporal glioma diagnosed by preoperative MRI
2	Glasgow score of 15 without preoperative symptomatic elevated intracranial pressure
3	New and/or recurrent intracranial gliomas are allowed
Exclusion Criteria	
1	Unable to comprehend and cooperate with the neurologic examination
2	Emergency craniotomy or changed to emergency from elective craniotomy
3	Insular lobe is invaded by glioma
4	Scheduled intraoperative motor evoked potential monitoring
5	Patients with traumatic brain injury, intracerebral hemorrhage, or cerebral vascular diseases
6	Patients with prolonged emergence, postoperative mechanical ventilation, and/or sedation dependence due to a definite reason (e.g., surgery itself or tumor location)
7	Hypothalamic dysfunction
8	Radiotherapy and/or chemotherapy before surgery
9	Uncontrolled hypertension or severe heart disease that impairs cardiac function (New York Heart Association Functional Classification ≥ III)
10	History of related anesthetic allergy
11	Severe endocrine system dysfunction that impair metabolic index
12	Impaired mental status
13	Drug and/or alcohol abuse
14	Pregnant and/or lactation period patients
15	Neuromuscular diseases
16	Infectious and/or immune diseases with positive biomarker(s)
17	Body mass index > = 35

Patients will be recruited in Beijing Tiantan Hospital, Beijing, China. The potentially eligible patient will be screened and contacted by a trial team member who explains the study and ascertains the patient’s interest 1 or 2 days before the scheduled operation day. If interested in enrolment, the patient will receive the detailed trial explanation and written consent form.

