### Discontinuation criteria

#### Massive hemorrhage or massive transfusion

Massive intraoperative bleeding can occur, and this study defines massive bleeding as blood loss exceeding the entire blood volume within 24 h from the start of operation or 50% of circulating blood volume loss within 3 h during operation requiring emergency intervention. Intraoperative massive transfusion (transfusion of more than 10 units of packed red blood cells) may be needed if massive hemorrhage is encountered. If bleeding occurs to this extent and meets either or both of the above criteria, the trial will be discontinued for this particular patient.

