#### Venous air embolism

Significant venous air embolism has been observed in rare cases, but neurosurgery carries the potential risk for this sometimes intractable complication, especially when the operative intervention occurs near venous sinuses or in the sitting position [12–14]. Venous air embolism may result in severe hypoxia and hypotension which can impair cerebral perfusion and oxygenation. If this happens, timely intervention and resuscitation needs to be carried out and the patient will be withdrawn from the trial. This will be reported as an adverse event.

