#### Postoperative coma

If the patient is in a coma (nonresponsive) after operation for any reason, the subject will not be able to cooperate with any neurological assessment, the subsequent follow-up will need to be discontinued, and this will be noted in the neurologic complication section. The patient will be withdrawn from the trial.

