### Statistical analysis plan

Kolmogorov-Smirnov testing will be used for evaluating if the continuous variables have a normal distribution or not. Descriptive statistics will be reported as means with standard deviation for normally distributed data; medians with interquartile range will be described for non-normally distributed data; for categorical variables, count (percentage) will be described. The difference in postoperative NIHSS scores at certain time points between the propofol and sevoflurance groups will be analyzed by t-test or Mann-Whitney U test depending on normal or non-normal distribution, respectively, and 95% confident interval will be determined for the NIHSS score change and difference between the two groups. The changes in VAS scores, intraoperative parameters, and stress response biomarkers over the observation time will be compared using repeated measurement, and post hoc analysis will be used for sensitivity analysis. For other secondary outcomes such as brain relaxation, MMSE score, anesthesia quality score and medical expense, the difference between the two groups will be analyzed by t-test or Mann-Whitney U test. All the categorical variables will be analyzed by chi-square testing. Missing data will be adjusted using inverse probability weighting and worst-case imputation scenarios. Statistical significance is defined as a type I error of 0.05, and the nature of the testing is two-tailed. Analyses will be conducted using Statistical Package for the Social Sciences (SPSS) version 17.0 (Chicago, IL, USA).

All data will be analyzed according to an intent-to-treat, such that all randomized patients originally allocated to the propofol or sevoflurane anesthesia arm at the time of randomization will be used for efficacy analysis. No interim analysis is planned. Worst observation carried forward method will be used to handle missing data.

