## Appendix

**Table 3 Tab3:** NIHSS and mNIHSS score system

Item	NIHSS	mNIHSS	Score
1a	LOC	[deleted]	0 = Alert 1 = Arousable by minor stimulation 2 = Arousable by strong/repeated stimulation 3 = Unresponsive
1b	LOC questions		0 = Answers both correctly 1 = Answers one correctly 2 = Answers neither correctly
1c	LOC Commands		0 = Performs both tasks correctly 1 = Performs one task correctly 2 = Performs neither task
2	Gaze		0 = Normal 1 = Parial gaze pulsy 2 = Forced deviation
3	Visual		0 = Normal 1 = Partial hemianopia 2 = Complete hemianopia 3 = Bilateral hemianopia
4	Facial Palsy	[deleted]	0 = Normal 1 = Minor 2 = Parial 3 = Complete
5a	Motor Arm (left)		0 = No drift 1 = Drift before 10s 2 = Falls before 10s 3 = No effort against gravity 4 = No movement UN = Amputation or joint fusion explain:
5b	Motor Arm (right)		
6a	Motor Leg (left)		
6b	Motor Leg (right)		
7	Limb Ataxia	[deleted]	0 = Absent 1 = In one limb 2 = In two Limb UN = Amputation or joint fusion
8	Sensory		In NIHSS: 0 = Normal 1 = Mild-to-Moderate loss 2 = Severe to total loss In mNIHSS: 0 = Normal 1 = Abnormal
9	Language		0 = Normal 1 = Mild-to-Moderate aphasia 2 = Severe aphasia 3 = Mute or global aphasia
10	Dysarthria	[deleted]	0 = Normal 1 = Mild-to-Moderate 2 = Severe UN=Intubated
11	Extinction and Inattention		0 = Normal 1 = Visual, tactile, auditory, spatial, or personal inattention 2 = Profound hemi-inattention or extinction to more than one modality

*NIHSS* National Institute of Health stroke scale, *mNIHSS* modified National Institute of Health stroke scale, *LOC* Level of Consciousness

The total score in NIHSS and mNIHSS are 42 and 31 respectively

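### Exclusion 6 and the withdrawal rules act after randomization and conflict with the all-randomized efficacy analysis, so extreme neurologic outcomes may be lost or mis-scored

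*Protocol article*

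**What the plan says.** All places are in the protocol article.

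- **Timing of randomization.** Under Randomization and blinding, patients who meet the Table 1 criteria are randomized, and the envelope stays sealed until the patient enters the operating room. Standard anesthetic management places assignment there too, before induction.
- **Exclusion 6 (Populations, Table 1).** "Patients with prolonged emergence, postoperative mechanical ventilation, and/or sedation dependence due to a definite reason"; the examples given are the surgery and the location of the tumor.
- **Exclusion 2 (same table).** "Emergency craniotomy or changed to emergency from elective craniotomy".
- **Discontinuation criteria.** For massive bleeding or transfusion, "the trial will be discontinued for this particular patient". For venous air embolism, "timely intervention and resuscitation needs to be carried out and the patient will be withdrawn from the trial". Anaphylaxis severe enough to stop the operation also leads to withdrawal. For postoperative coma of any cause, the stated reason is that "the subject will not be able to cooperate with any neurological assessment"; follow-up stops, the event is noted as a neurologic complication, and the patient is withdrawn.
- **Scale (Appendix, Table 3, item 1a).** The top category for level of consciousness is "3 = Unresponsive".
- **Study endpoint.** The primary endpoint is the NIHSS change within 4 h, taken when OAA/S reaches 4.
- **Analysis set (Statistical analysis plan).** Under intent-to-treat, "all randomized patients originally allocated to the propofol or sevoflurane anesthesia arm at the time of randomization will be used for efficacy analysis". The same section names inverse probability weighting and worst-case imputation for missing data and then, separately, worst observation carried forward.

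**The concern.** The trial asks whether two anesthetics leave the same residual effect on early neurologic function. A patient who does not wake, or wakes very late, is at the extreme of that outcome. Exclusion 6 and the coma rule act on exactly these patients, after they have been allocated and treated.

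Exclusion 6 also depends on someone deciding that there was a definite reason for the delay. The article gives no definition and names no blinded assessor for that decision, and the anesthesiologists know the allocation.

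The analysis section promises to use everyone randomized. The article does not say how a patient caught by exclusion 6, or withdrawn before any postoperative score, enters that analysis. An equivalence conclusion could then depend on how a small number of extreme patients are treated, and that choice would be open after the data are seen.

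**Working it through.** **1. The passages side by side**

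| Rule | When it can be known | What happens | Analysis section |
|---|---|---|---|
| Exclusion 6 | As worded, during or after emergence | Not eligible | Already randomized, so included |
| Exclusion 2, conversion part | Before or after allocation | Not eligible | Included if already randomized |
| Haemorrhage, severe anaphylaxis, air embolism | After allocation | Discontinued or withdrawn | Included |
| Coma | After surgery | Follow-up stops, withdrawn | Included |

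**2. What the missing-data rules do with a comatose patient**

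Suppose follow-up stops before any postoperative score. The only observation is the baseline, so under worst observation carried forward the change is baseline − baseline = 0. Worst-case imputation would assign a poor score instead. Inverse probability weighting would give the patient no score and reweight the others. The three answers differ and no order of priority is stated. A patient who does not reach OAA/S 4 within 4 h also has no defined primary value.

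**3. The plan's own figures**

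The Sample size calculation gives a difference of 0.5, SD 1.5, margin 1.0, 80% power and 160 per group, raised to 176. The usual formula at one-sided 0.025 gives

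n = 2 × 1.5² × (1.960 + 0.842)² / (1.0 − 0.5)² ≈ 141.3, so 142 per group.

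At one-sided 0.05 it gives 112. The stated 160 is therefore not reproduced; it is larger than these formulas require. This point does not depend on that. Only the SD of 1.5, the margin of 1.0 and 176 per group are used below.

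**4. Effect on the mean difference**

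Let L be the extra NIHSS worsening in affected patients. Event rates and L are not in the document and are assumed.

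Shift in difference = (excess events in one arm / 176) × L

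- No excess: 0 × L = 0, no shift.
- 5 excess events, L = 10: 5/176 × 10 = 0.28.
- 5 excess events, L = 20: 5/176 × 20 = 0.57, more than the 0.5 between the assumed difference and the margin.
- 9 excess events, L = 20: 9/176 × 20 = 1.02, about the whole margin.

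The sign depends on which arm has the excess and on the sign of the difference among the remaining patients.

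**5. Effect on the variance when rates are equal**

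SD with the events kept = √(1.5² + r(1 − r)L²), where r is the common event rate.

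- r = 2%, L = 10: √(2.25 + 0.02 × 0.98 × 100) = √4.21 = 2.05.
- r = 5%, L = 20: √(2.25 + 0.05 × 0.95 × 400) = √21.25 = 4.61.

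Half-width of the 95% confidence interval at 176 per group = 1.967 × SD × √(2/176):

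- SD 1.5: 0.31
- SD 2.05: 0.43
- SD 4.61: 0.97

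Power for equivalence (one-sided 0.025, true difference 0.5, 176 per group) is about 88% with SD 1.5 and about 63% in the 2% and 10-point case. In the 5% and 20-point case it is below 10%. Leaving these patients out, or scoring them as unchanged, therefore makes equivalence easier to declare even when the arms do not differ in event rate.

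**The case against.** The strongest reply has four parts.

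- **Withdrawn does not mean dropped from the analysis.** The discontinuation criteria end participation or follow-up, and none of them removes a patient from the analysis set. Worst-case imputation would give a comatose patient a poor score, and coma is recorded as a complication. This stands. A reader might infer that the worst outcomes are deleted, but the document does not say so. What it leaves is an unresolved conflict, because one of the named methods can score such a patient as no change.
- **Exclusion 6 may have meant anticipated problems.** Tumor location is known beforehand, the criteria are applied at randomization, and both examples are non-anesthetic causes. Late waking without such a cause is not excluded by its terms. This partly stands, but the text does not say anticipated or planned, and surgery as a cause is not known before surgery.
- **Bias toward equivalence is not certain.** A reader might infer that each removal shrinks the difference. It does not: with equal rates and severity there is no shift, and otherwise the shift can go either way. Haemorrhage, anaphylaxis and air embolism are not neurologic outcomes in themselves, and bleeding that meets its 24 h criterion late may come after the primary score has been taken.
- **No per-protocol set is described.** A reader might count this as a gap in an equivalence trial. A condensed article commonly leaves it to a fuller plan, so it is not part of this point.

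**Conclusion.** The conflict is real and rests on the article's own text. Eligibility and withdrawal rules act after randomization, the analysis set includes everyone randomized, coma is called unassessable although the scale codes it, and the missing-data methods are unranked. Coma and prolonged emergence carry most of the weight.

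The risk is loss or mis-scoring of extreme neurologic outcomes. Its size cannot be fixed from the document. It ranges from no shift, if events are balanced, to about 0.57 points with 5 excess events among 176 at an assumed 20 points each. With 2% events at an assumed 10 points in both arms, the SD is understated as 1.5 instead of about 2.05. The text does not support the stronger conclusion that these patients will be dropped and that this must favour equivalence. The passages should be reconciled before the data are analysed.

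**What to change.** 1. Reword exclusion 6, and the conversion part of exclusion 2, so that they refer only to what is known or planned before randomization.
2. In all four discontinuation criteria, separate stopping study procedures from stopping outcome collection. Continue NIHSS assessment where possible, score unresponsive patients on the scale, and keep every randomized patient in the primary analysis. Clinical management is not affected.
3. State one primary rule for patients who do not reach OAA/S 4 within 4 h or have no postoperative score. Say openly that this extends the definition under Study endpoint. Use the other missing-data methods as sensitivity analyses.
4. Report these events by arm, including any exclusion 6 cases found after allocation.

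The cost is protocol wording, an amendment and some further assessments. The statistical downside is that a few high scores may widen the confidence interval, possibly materially, and lower power: from about 88% to about 63% in the 2% and 10-point illustration, and much further in the 5% and 20-point one. The sample size should be looked at again once the scoring rule is chosen.

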### Randomization and blinding

Permuted-block randomization will be used with a block size of 4 and an allocation ratio of 1:1 to either sevoflurane-remifentanil group or propofol-remifentanil group. Random allocation sequence will be based on a computer-generated random digits table. One investigator who will not participate in anesthetic management or follow-up will implement the randomization and enroll patients, and allocation will be concealed in a sealed opaque envelope until patient enters the operating room. Randomization will occur for patients conforming to the above criteria, and written informed consent will then be obtained from themselves or their next-of-kin. Since the two general anesthetic administration routes are distinct (inhalational versus intravenous), patients and anesthesiologists cannot be blinded. An independent team who is not involved in the intraoperative management will be in charge of postoperative follow-up and is blinded to the intervention.

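### A fixed, published block size of 4, with one investigator both randomizing and enrolling, lets someone who knows the block so far deduce up to a third of allocations

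*Protocol article*

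**What the plan says.** Under Randomization and blinding, the protocol article fixes the scheme: "Permuted-block randomization will be used with a block size of 4", with 1:1 allocation. No stratification factor is given. On roles, it says: "One investigator who will not participate in anesthetic management or follow-up will implement the randomization and enroll patients". The allocation stays in a sealed opaque envelope until the patient reaches the operating room.

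Trial design describes a single-center, "open label, randomized parallel arm equivalent clinical trial". Randomization and blinding adds that "patients and anesthesiologists cannot be blinded", so the arms of past patients are known on site. Postoperative follow-up is done by a separate, blinded team.

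Three further statements bear on timing and safeguards:
- Populations puts screening and first contact 1 or 2 days before surgery.
- Populations also requires the reasons why eligible patients are not recruited to be documented.
- Standard anesthetic management places assignment on the day of operation, at admission to the operating room.

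**The concern.** An opaque envelope hides its own contents. It does not hide what earlier allocations imply about the next one. With one site, no stated strata and a known block of 4, there is a single running sequence, and each block must end with two patients per arm. Anyone who follows the arms of past patients can sometimes tell which arm comes next. The same investigator implements the sequence and enrolls, so the text does not separate knowledge of the sequence from the decision to enroll.

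What is at stake is selection: whether a patient with, say, an unfavorable tumor location or an expected difficult course enters when a particular arm is due. Such selection would act on early NIHSS change. Sample size calculation sets an equivalence margin of 1.0 and assumes a true difference of 0.5, which leaves 1.0 − 0.5 = 0.5 points of room. A modest imbalance in prognosis could therefore matter in either direction. The article gives nothing from which the size of such a bias could be computed, and none is claimed here.

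**Working it through.** The article states no predictability figure, so there is none to reproduce.

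**Inputs.** Block size 4, ratio 1:1 (Randomization and blinding); 352 patients (Sample size calculation), hence 352 / 4 = 88 blocks; recruitment from 28 May 2018 to 31 December 2020 (Trial status), which is 948 days; approach 1 or 2 days before surgery (Populations).

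**Step 1: full knowledge of the block.** A 2+2 block has C(4,2) = 6 equally likely orders, so 24 positions in all. An allocation is certain once one arm's two places are used up. The best guess is the arm with more places left, or a coin toss if they are equal.

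| Position | P(certain) | P(best guess correct) |
|---|---|---|
| 1 | 0 | 1/2 |
| 2 | 0 | 2/3 |
| 3 | 1/3 | 1/3 × 1 + 2/3 × 1/2 = 2/3 |
| 4 | 1 | 1 |

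- Certain: (1/3 + 1) / 4 = 8/24 = 33.3%, and 352 × 1/3 ≈ 117 patients.
- Best guess: (1/2 + 2/3 + 2/3 + 1) / 4 = 17/24 = 70.8%, or about 249 of 352, against 176 by chance.

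**Step 2: knowledge at the time of approach.** If one earlier patient's envelope is still unopened, only position 4 can be certain, and only when the first two allocations match: (1/3) / 4 = 1/12 = 8.3%. With two unopened, the share is 0%.

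Accrual is 352 / 948 = 0.371 per day, or 2.6 per week. Assume Poisson arrivals, with the number of pending patients having mean m = 0.371 × lead time in days. The certain share is then e^(−m) × 1/3 + m e^(−m) × 1/12.

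- 1-day lead: m = 0.371; 0.690/3 + 0.256/12 = 0.251, about 88 patients.
- 2-day lead: m = 0.743; 0.476/3 + 0.353/12 = 0.188, about 66 patients.

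Populations also allows consent a few days ahead; a longer lead lowers the share further.

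**Step 3: effect of changing the blocks.** A fixed, known block of 6 gives 25% certain and a 68.3% hit rate; a block of 8 gives 20% and 66.6%. For randomly varying sizes, the simulated observer knows the set of sizes but not the size of the current block, and sizes are equally likely:

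| Sizes | Certain | Best guess |
|---|---|---|
| 4 fixed | 33.3% | 70.8% |
| 4, 6 | 5.6% | 69.3% |
| 4, 6, 8 | 2.5% | 68.0% |

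Varying the size removes most of the certainty but under 3 percentage points of the guessing advantage.

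**The case against.** The strongest reply is that the one-third figure needs an observer who knows the block boundaries and every earlier arm in the block at the moment of decision. Patients are on an elective list and are approached before their own and any pending envelopes are opened. Nothing shows that the enroller sets operation dates or their order. The enroller has no part in anesthetic management or follow-up, so need not see past arms. First contact is made by a trial team member who is not expressly the randomizing investigator. Recording reasons for non-recruitment makes selective refusal open to audit. Implementing the randomization need not mean holding the list, and a condensed article may leave custody to the full protocol.

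Most of this stands as a limit on size. It makes one third a ceiling and 19% to 25% the fairer range at approach. It does not remove the point: block size, single center, open label and the dual role are all stated choices. The safeguards protect conduct and assessment, or help detect selection afterwards; none prevents deduction from a known block. Timing is also not settled, because Randomization and blinding places written consent after randomization, while Populations places it before the day of surgery.

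A reader might also infer that the blinded follow-up team could guess arms within a block. The article does not support this: a team that does not know the earlier arms has nothing to extrapolate from.

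**Conclusion.** The point holds as an avoidable weakness in concealment. With a fixed, published block of 4 and one person both implementing the sequence and enrolling, up to 33.3% of allocations (about 117 of 352) could be deduced and 70.8% guessed. This assumes full knowledge of the block and applies at operating-room entry. At approach 1 to 2 days earlier the certain share is about 19% to 25%, under Poisson accrual at the planned rate.

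Three stronger readings go too far:
- **That a third of allocations are predictable without conditions.** The figure depends on what the decision-maker knows and when.
- **That the enroller sees the whole sequence.** This would follow only if that person held the list, and the article does not say who does.
- **That any resulting bias is beyond repair in analysis.** Baseline NIHSS and MRI lesion details are collected (Outcomes), so selection on those could be adjusted for. Selection on unmeasured factors could not.

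Nothing in the article shows that allocations were in fact predicted.

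**What to change.** For whatever part of the sequence remains:

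1. Generate it with randomly varying block sizes, for example 4, 6 and 8, and do not disclose the sizes to site staff. Certain allocations fall to about 2.5% and the best-guess rate to about 68%.
2. Have the list and sequentially numbered opaque envelopes prepared and held by an existing team member who does not screen, consent or enroll. This is needed because step 1 leaves most of the guessing advantage in place.

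The cost is a new list, one reassigned task and an amendment through the route under Protocol amendment. No extra staff should be needed, although the article does not describe staffing, so that is an assumption. The statistical downside is small: stopping inside a block of 8 could leave the arms unequal by at most 4 patients, against at most 2 inside a block of 4.

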### Interventions

#### Standard anesthetic management

On the day of operation, patients will be admitted into the operating room to be randomly assigned into either the sevoflurane-remifentanil or propofol-remifentanil group. Vital signs including electrocardiography (ECG), blood pressure (BP), heart rate (HR), pulse oxygen saturation (SpO2), end-tidal carbon dioxide (ETCO_2_), body temperature, and urine output will be monitored throughout the study. 100% fraction of oxygen will be provided by mask to the patients for preoxygenation for 5 min prior to anesthetic induction. No premedication will be given.

All patients will be induced with 0.3 μg/kg sufentanil, 2–2.5 mg/kg propofol, and 0.7–0.8 mg/kg rocuronium or cisatracurium. After tracheal intubation, mechanical ventilation will be established, at a tidal volume of 8-10 ml/kg, respiratory rate of 12–15/min, inspiratory:expiratory ratio of 1:2, fraction of inhaled fresh oxygen as 60%, and flow rate of fresh gas as 1.5 L/min. After induction, anesthesia will be maintained according to one of the two group allocations: (1) 6-8 mg/kg propofol with 0.05–0.2 μg/kg remifentanil for the propofol group or (2) 1.3–1.5 Minimum Alveolar Concentration (MAC) sevoflurane with 0.05–0.2 μg/kg remifentanil for the sevoflurane group. The dosage of anesthetic will be adjusted according to the bispectral index (BIS) value, which will be maintained between 40 and 60. 0.5% ropivacaine 1 to 2 mL for each injection point will be used for scalp nerves block before the start of surgeries. Sufentanil 5–10 mcg can be given, by anesthesiologist discretion, to alleviate potent stress responses when head pins are placed or scalp incision is performed, based on the hemodynamic parameters. Additional sufentanil bolus at the dose of 5-10mcg during operation is allowed, the last bolus should be given ahead of at least 60 min before expected end of surgery. The muscle relaxant cisatracurium will be infused at 0.1 mg/kg/h during the operation for all patients and stopped once the bone flap is secured. Propofol and sevoflurane will be reduced according to BIS and hemodynamic parameters once the bone flap is fixed and stopped at skin dressing.

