### Study endpoint

The primary endpoint will be NIHSS score change within 4 h after general anesthesia by sevoflurane-remifentanil or propofol-remifentanil when observer’s assessment of alertness/sedation (OAA/S) reaches 4. The time to reach OAA/S score of 4 at the first time point will be recorded.

Secondary endpoints will be as follows:
The NIHSS score change at postoperative day 1 and postoperative day 2 from the baseline, the level of OAA/S in these two time points will be recorded.Hemodynamic stability including blood pressure, heart rate, episodes of hypertension, hypotension, tachycardia, and bradycardia;Intraoperative brain relaxation (Brain relaxation assessed immediately after opening of the dura on a scale ranging from 1 to 4 (1 = perfectly relaxed, 2 = satisfactorily relaxed, 3 = firm brain, 4 = bulging brain);Quality of anesthesia emergence including time of eye opening, time of emergence, coughing during extubation, postoperative nausea and vomiting (PONV), shivering, and agitation;Quality of anesthesia recovery assessed by QoR-40 at postoperative day 2;Changes of cognitive function at postoperative day 2 assessed by MMSE;Postoperative pain at PACU, 1, and 2 days after surgery evaluated by VAS;Postoperative neurological complications (e.g., intracranial hematoma, infection, seizure etc.);Anesthesia expenses and in-hospital total expenses;

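### The blind covers only postoperative follow-up, so brain relaxation and, more weakly, early emergence items are rated outside it, and masking of the OAA/S 4 call that times the primary NIHSS is not secured

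*Protocol article*

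**What the plan says.** The section Trial design describes a "prospective, single-center, open label, randomized parallel arm equivalent clinical trial". Under Randomization and blinding, the different routes of administration are given as the reason why "patients and anesthesiologists cannot be blinded". The same section then defines the blind: "An independent team who is not involved in the intraoperative management will be in charge of postoperative follow-up and is blinded to the intervention". The surgeon is not mentioned.

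The section Study endpoint lists outcomes that arise at different moments:

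- Brain relaxation: "Brain relaxation assessed immediately after opening of the dura on a scale ranging from 1 to 4".
- Emergence: "Quality of anesthesia emergence including time of eye opening, time of emergence, coughing during extubation, postoperative nausea and vomiting (PONV), shivering, and agitation".
- The primary NIHSS change, taken within 4 h after anesthesia once OAA/S is 4, with the added instruction: "The time to reach OAA/S score of 4 at the first time point will be recorded".

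No rater is named for any of these in that section. The section Data collection and management says that the anesthesiologists on the follow-up team hold NIHSS certification. On the study agents, Standard anesthetic management says: "Propofol and sevoflurane will be reduced according to BIS and hemodynamic parameters once the bone flap is fixed and stopped at skin dressing".

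**The concern.** The blind is defined by the phase of care, but the endpoints are not confined to that phase. A team that takes no part in intraoperative management and works postoperatively cannot, as worded, be the rater of something judged at dural opening. That grade runs from a fully relaxed to a bulging brain. It is a matter of judgement, and a rater who knows the agent may lean toward an expected answer. The early emergence items occur under an anesthesiologist whom the article declares unblinded.

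The primary endpoint is affected in a more limited way. The OAA/S 4 call fixes when the NIHSS is scored, and so how much residual sedation it may capture. The scale in the appendix includes level-of-consciousness items (1a to 1c). If the person making that call knew the arm, the timing could differ between arms even with a blinded NIHSS rater. The trial hopes to show equivalence, so a small systematic shift toward zero would favor its hypothesis.

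**Working it through.** The article gives no figure on masking, so there is none to reproduce. The check sets each outcome against the stated scope of the blind.

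| Outcome | When it arises | Rater stated | Inside the blind as worded? |
|---|---|---|---|
| Brain relaxation, 1 to 4 | At dural opening, agent running | None | No |
| Eye opening, emergence time, cough at extubation | At emergence, after the agents stop at skin dressing | None | Not stated; the period is managed by the unblinded anesthesiologist |
| PONV, shivering, agitation | At emergence or later | None | Possibly; they need not be rated in the operating room |
| OAA/S 4 call | Within 4 h after anesthesia | None; no place given | Not secured |
| Primary NIHSS | At OAA/S 4 | Certified raters are on the follow-up team | Apparently yes |

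**Brain relaxation.** The conclusion needs two sentences of the article: the definition of the blinded team and the time of the grading.

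**Primary NIHSS.** Randomization and blinding makes the follow-up team blinded, and Data collection and management makes its anesthesiologists the certified raters. Together they indicate blinded scoring. By then the agents have been stopped, and the endpoint list places at least one early assessment (pain) in the PACU. What remains open is who makes the OAA/S 4 call, and where.

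**Illustration of sensitivity (the bias is assumed).** The documents give no size for rater bias, so a range of b = 0.1 to 0.3 NIHSS points is assumed. Inputs from Sample size calculation: SD 1.5, margin 1.0, anticipated difference 0.5, 160 per group.

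- Standard error of the difference: SE = 1.5 × √(2/160) = 0.168.
- True difference at the margin (1.0), shift b toward zero: P(declare equivalence) ≈ Φ(b/SE − z), with z = 1.645 (one-sided 0.05) or 1.960 (one-sided 0.025).
- True difference 0.5, shift b away from zero: P ≈ Φ((1.0 − 0.5 − b)/SE − z).

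| b | True difference 1.0, toward zero: 0.05 / 0.025 | True difference 0.5, away from zero: 0.05 / 0.025 |
|---|---|---|
| 0 | 0.050 / 0.025 | 0.909 / 0.846 |
| 0.1 | 0.147 / 0.086 | 0.770 / 0.665 |
| 0.2 | 0.326 / 0.221 | 0.557 / 0.432 |
| 0.3 | 0.557 / 0.432 | 0.326 / 0.221 |

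The table shows that this design is sensitive to small shifts in either direction. It does not show that any shift exists. The figure of 160 per group is used only as an input. Whether it follows from its own assumptions is a separate question on which this point does not depend.

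**The case against.** The strongest reply is that the article is candid. It calls the trial open label, says who cannot be blinded, and claims blinding only for postoperative follow-up. It never promises masked intraoperative ratings. It is also a condensed account, and who rates each item may stand in the full protocol, so silence about a rater is not in itself an error. This stands for the unnamed raters. It does not dispose of brain relaxation, because the article itself fixes the scope of the blind, and that scope leaves out an endpoint the article lists.

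A second reply is that eye opening and cough at extubation are observed events rather than graded judgements, and that agitation can be rated later by the blinded team. This is fair, and is why the emergence items carry less weight.

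A reader might go further and infer that the OAA/S 4 call is made in the operating room with the agent on view, so that the primary endpoint is in effect unblinded. The documents do not support that. The agents have been stopped by then, the window is 4 h, a PACU assessment exists, and the certified raters sit on the blinded team. That team may well make the call in the PACU. Scoring at a common OAA/S level also limits differences in sedation between arms, provided the call is made alike in both. A reader might also take the unblinded surgeon as a fact; the article neither names the surgeon as rater nor says the surgeon is told the allocation.

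**Conclusion.** The point holds in a limited form. As written, brain relaxation is rated outside the blind, and the early emergence items are so more weakly. These are secondary endpoints. For the primary NIHSS, blinded scoring appears to be in place; only the masking of its timing is not secured, because the rater and place of the OAA/S 4 call are not stated. The size and direction of any bias are unknown. The probabilities in the illustration rest on assumed shifts and only show why a small one would matter with a margin of ±1. This is a cheap improvement to the masking scheme, not a flaw that undermines the primary comparison.

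**What to change.** Amend Randomization and blinding as follows.

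1. The operating neurosurgeon grades brain relaxation, is not told the allocation, and has the vaporizer and infusion pump screened from view.
2. The existing blinded team makes the OAA/S 4 call as well as the NIHSS score, away from the anesthetic workstation, with the anesthesia record withheld until the score is entered.
3. Emergence items rated by the anesthesiologist are reported as unblinded.

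The cost is protocol wording and a screen, with no added staff. The small downside is that, in patients alert before they leave the operating room, the blinded OAA/S and NIHSS assessment may come a few minutes later.
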